[figure not shown]

**7. Were there any applications for ethical approval concerning the same issue?**

No.

1. **Study Procedures:**
2. **Aim of study, objective, hypothesis**

Accumulation of intracranial air is one of accompanying appearances following cranial surgeries (Reasoner et al., 1994).Small amount of intracranial air is reabsorbed completely within days or weeks, and in most instances, no clinical sign or symptom was observed. Accumulation of large amounts of intracranial air is rare, however, it can develop into a serious emergency situation, particularly if air pressure increases, so-called tension pneumocephalus, and compresses the brain and the cranial nerves extensively (Markham JW, 1967; Standefer et al., 1984), and even life-threatening brainstem compression or brain herniation (Biyani et al., 2006).

Surgical interventions in the semisitting position are intended to optimize surgical conditions by reducing bleeding in the operation field, reducing brain swelling, providing a clean view of the surgical field, and improving the surgical approach. The gravitational effects contribute the better anatomical orientation and less brain retraction (Hermann et al., 2008; Porter et al., 1999). There are, however, some potentially life-threatening risks associated with surgery in the semisitting position, among others, pneumocephalus (Kitahata et al., 1976, MacGilliverg, 1982, Toung et al., 1983, Standefer et al., 1984).

Asymptomatic pneumocephalus would be reabsorbed spontaneously within 1 to 3 weeks (Di Lorenzo et al., 1986). Large symptomatic intracranial air might require emergency twist-drill or burr hole craniostomy to remove the entrapped air. This procedure is associated with additional morbidity and surgical risks.

Normobaric oxygen has been suggested to be effective to treat pneumocephalus, since oxygen is able to replace nitrogen by increasing the diffusion gradient for nitrogen between the air collection and the surrounding tissue (Dexter & Reasoner, 1996). Using a mathematical model, proposed by Dexter and Reasoner in 1996, a FiO2 of 100% would be necessary to achieve significant air absorption within hours to days (Dexter & Reasoner, 1996). This model suggests that air would be resorbed faster if there is a greater gradient in the concentration of molecules between air and blood. The air resorption rate would be higher if there is less N2 dissolved in the blood of capillary arteries in the adjacent cerebral tissue. In 2008, Gore et al. demonstrated a significant increase of pneumocephalus resorption in 6 patients, who had normobaric hyperoxia at FiO2 68% over a non-rebreather mask for a period of 24 hours, resulting in a significant mean air volume reduction (Gore et al., 2008).

Considering that, we aimed to analyze the effect of administration of normobaric hyperoxia at FiO2 100% over an endotracheal tube (ETT) for 3 hours on pneumocephalus after posterior fossa surgery in the semisitting position. If higher air resorption rate were to be confirmed, a novel therapy approach will be established to reduce the postoperative morbidity.

Routine cranial CT scans with a secondary reconstruction of the volume of intracranial air will be performed immediately and 24 hours after surgery.

To assess the clinical state, patients will be requested to indicate their own level of sleepiness according to the Stanford Sleepiness Scale (Hoddes et al., 1973). Moreover, possible temporary frontal lobe dysfunction which correlates to pneumocephalus, will be assessed using the Stroop color-word interference test (Stroop JR, 1935; Eigelsreiter et al., 1986). The collected data and images will be compared and analysed.

1. **Study objectives**

The aim of this prospective randomized controlled trial is to prove, whether administration of normobaric hyperoxia at FiO2 100% might accelerate the resorption of postoperative supratentorial pneumocephalus after posterior fossa surgery in the semisitting position.

A total of 44 patients aged 18 to 80 years will be randomized and evaluated after written informed consent are obtained. Patients randomized to the treatment group will be ventilated with normobaric hyperoxia at FiO2 100% via the endotracheal tube (ETT). Patients randomized to the control group will be weaned off from ventilation and will then be extubated.

The primary objective of this study consists of two co-primary endpoints. The first co-primary endpoint is the mean change of air volume between CT scan performed immediately and 24 hours after completion of surgery. The second co-primary endpoint is the air resorption rate, which is defined as the mean change of air volume divided by the time between the two CT scans.

Furthermore, the efficacy of normobaric hyperoxia at FiO2 of 100% on attention, as measured by the Stroop color-word interference tests, and on alertness, as noted on the Stanford Sleepiness Scale, will be compared and analyzed.

**3. Randomization procedure**

Patients meeting the inclusion criteria will be randomized to treatment or control group after measurement of the air volume in cranial CT scan which will be performed immediately after completion of surgery. The randomization will be conducted independently from the patient recruitment at the Institute of Biostatistics. The Stroop color-word interference test will be performed one day before surgery and 24 hours after surgery by an Investigator, which is blinded to the treatment group.

1. **Patients selection**

We hypothesized that patients who will be treated with normobaric hyperoxia at FiO2 100% via endotracheal tube for 3 hours will show a significantly volume change and a higher resorption rate of postoperative pneumocephalus as compared to untreated patients. It is assumed, that there are no drop-outs in this trial.

Sample size is calculated based on the study by Gore et al (2008). In this study, 6 patients, who had normobaric hyperoxia at FiO2 68%, over a non-rebreather mask for a period of 24 hours, were compared to 7 patients who were breathing room air. Assuming a two-sided type I error of 5% and a power of 90%, for the mean change of pneumocephalus a total of 22 patients per study group (difference:16.6, common SD: 16.3) and for the mean air absorption rate (difference:1.37, common SD: 0.96) a total of 12 patients per study group are considered necessary. Subsequently, a total of 44 patients are necessary for recruitment. Moreover, it is assumed that the ANCOVA may enhance the statistic power.

**5. Statistical consideration**

Baseline characteristics (quantitative parameters: mean, standard deviation (SD), range; qualitative parameters: absolute and relative frequencies) will be compared descriptively using two-sided t-tests or χ2 tests.

Both primary endpoints will be analysed using an analysis of covariance (ANCOVA) including the respective baseline values. A 95% confidence interval for the treatment effect (control – treatment) and the corresponding p-values will be calculated from the ANCOVA model. A two-sided p-value less than 0.05 is considered statistically significant. Estimates of the mean change and respective standard errors (SE) from the ANCOVA model per study group will be calculated. Sensitivity analysis including gender and age (dichotomized by the respective median) and the respective subgroups will be reported separately.

Differences in mean time for the Stroop color-word interference tests (postoperative – preoperative) will be analyzed in line with the primary endpoints. In addition no failure versus one or more failures in word reading/colour naming will be compared between the treatment and control group using descriptive χ2 tests.

The Stanford Sleepiness Scale will be analysed using descriptive two-sided t-test and Fisher’s exact test.

1. **Inclusion criteria**

Primary inclusion criteria are patient’s age above 18 years, who will undergo posterior fossa surgery in the semi-sitting position (as performed routinely in ours institution). Surgery must be performed with standard anaesthetic and ventilation procedures. Postoperative course must be uneventful without any complication. CT scan should show intracranial air collection of 30 ml or more.

1. **Exclusion criteria**

Patients with a history of any cardiac disease or previously cardiac surgery, any pulmonary disease, chronic obstructive pulmonary disease (COPD), chronic cough or dyspnoe, abnormal chest X-ray, or previously pulmonary surgery are not considered for this study.

Patients, who will need, for whatever reason, a CSF drain or prolonged postoperative ventilation, will be excluded.

Pregnant or breastfeeding women will also be excluded.

1. **Discontinue criteria**

Patients may discontinue from participation in this study at any time without giving any reasons.

1. **Special formalities**

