**Time: First task ____________ sec Mistakes: First task ___________**

**Investigator: _____________________**

## Color-word interference test (preoperative)

Second task – color name

Please name the color of the letters independently of the written word as fast as possible. The time will be measured and mistakes will be marked (X over the words).

Name: _________________________ Date: __________ ___________

| **Red** | **Blue** | **Yellow** | **Green** | **Yellow** | **Green** | **Yellow** | **Red** | **Green** | **Red** |
| --- | --- | --- | --- | --- | --- | --- | --- | --- | --- |
| **Blue** | **Green** | **Red** | **Yellow** | **Red** | **Green** | **Green** | **Blue** | **Red** | **Yellow** |
| **Green** | **Blue** | **Red** | **Blue** | **Blue** | **Red** | **Green** | **Blue** | **Green** | **Blue** |
| **Yellow** | **Green** | **Red** | **Green** | **Yellow** | **Red** | **Blue** | **Red** | **Blue** | **Red** |
| **Red** | **Yellow** | **Red** | **Green** | **Green** | **Blue** | **Red** | **Yellow** | **Blue** | **Green** |

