**Time: Second task ____________ sec Mistakes: Second task ___________**

**Investigator: _____________________**

## Color-word interference test (postoperative)

First task – word name

Please read the written color names of the words independently of the color of the ink as fast as possible. The time will be measured and mistakes will be marked (X over the words).

Name: _________________________ Date: __________ ___________

| **Red** | **Blue** | **Yellow** | **Green** | **Yellow** | **Green** | **Yellow** | **Red** | **Green** | **Red** |
| --- | --- | --- | --- | --- | --- | --- | --- | --- | --- |
| **Blue** | **Green** | **Red** | **Yellow** | **Red** | **Green** | **Green** | **Blue** | **Red** | **Yellow** |
| **Green** | **Blue** | **Red** | **Blue** | **Blue** | **Red** | **Green** | **Blue** | **Green** | **Blue** |
| **Yellow** | **Green** | **Red** | **Green** | **Yellow** | **Red** | **Blue** | **Red** | **Blue** | **Red** |
| **Red** | **Yellow** | **Red** | **Green** | **Green** | **Blue** | **Red** | **Yellow** | **Blue** | **Green** |

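### Stroop mistakes are reduced to none versus any and the recorded preoperative count is not used, which costs precision in a secondary comparison but causes neither bias nor an invalid test

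*Combined protocol and SAP*

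**What the plan says.** All references are to the combined protocol and SAP.

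- **Timing.** Under 3, Randomization procedure: "The Stroop color-word interference test will be performed one day before surgery and 24 hours after surgery by an Investigator". Randomization follows the CT scan made directly after surgery, so the preoperative Stroop result is a true pre-randomization baseline.
- **Recording.** Each form prints a grid of 5 rows by 10 columns, so a task has 50 words. Wrong words are crossed, and a number is entered per task ("Mistakes: First task", "Mistakes: Second task") on both the preoperative and the postoperative forms.
- **Stroop time.** Under 5, Statistical consideration: "Differences in mean time for the Stroop color-word interference tests (postoperative – preoperative) will be analyzed in line with the primary endpoints". For those endpoints the plan states: "Both primary endpoints will be analysed using an analysis of covariance (ANCOVA) including the respective baseline values".
- **Stroop mistakes.** The next sentence reads "In addition no failure versus one or more failures in word reading/colour naming will be compared between the treatment and control group" and ends "using descriptive χ2 tests". It mentions no preoperative value. It also leaves open which visit is meant, whether the two tasks are tested separately or pooled, and whether a continuity correction applies.
- **Status.** The study flow chart lists the Stroop test as a secondary endpoint.

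**The concern.** Two results of the same test, taken at the same two visits, are treated differently without a stated reason. Time keeps its full scale and is adjusted for baseline; mistakes do neither.

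Under none/any, one slip in 50 words counts the same as twenty. A patient who made as many mistakes the day before surgery counts the same as one who has newly deteriorated. Both features add noise to a comparison with only 22 patients per arm. At stake is the trial's ability to see an effect on accuracy in its attention test. The primary conclusion and the sample size do not depend on it.

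**Working it through.** **1. The group size.** The plan sizes the trial on the co-primary endpoints (two-sided 5%, power 90%) and gives no figure for Stroop mistakes. With n = 2(1.960 + 1.282)² × (SD/difference)² per arm:

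- volume change: 21.0 × (16.3/16.6)² = 20.3, so 21; the t-based calculation gives 21.3, so 22;
- absorption rate: 21.0 × (0.96/1.37)² = 10.3, so 11; the t-based calculation gives 11.4, so 12.

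The stated 22 and 12 are reproduced by the t-based calculation. With no drop-outs assumed, the Stroop comparison has 22 per arm.

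**2. Is the chi-square test valid at 22 per arm?** An expected cell count falls below 5 when 22p < 5, that is, when the pooled rate is below 22.7% or, by symmetry, above 77.3%. The true type I error was found by summing the probabilities of all 23 × 23 possible outcomes at nominal 5%:

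| Common mistake rate | Pearson, uncorrected | Fisher's exact |
|---|---|---|
| 5% | 0.0148 | 0.0027 |
| 10% | 0.0432 | 0.0144 |
| 20% | 0.0515 | 0.0242 |
| 30% | 0.0481 | 0.0238 |
| 50% | 0.0490 | 0.0229 |
| Maximum over all rates | 0.0519 | 0.0244 |

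The uncorrected test holds its level throughout and is conservative at the extremes. Fisher's test would cost power: 43% against 55% for rates of 50% versus 20%, and 28% against 39% for 30% versus 10%.

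**3. How much precision is lost?** The documents give no mistake rates, so every input here except the 22 per arm is an assumption. Postoperative counts are Poisson with mean m in controls and m/2 under treatment, multiplied by a log-normal patient factor (SD 0.8 on the log scale). Preoperative counts have mean 0.6m. The patient factors before and after surgery correlate at 0, 0.5 or 0.8. Power at two-sided 5%, from 2,000 runs per row:

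| m | Controls with a mistake | Correlation | None/any chi-square | Wilcoxon on counts | Rank ANCOVA with baseline |
|---|---|---|---|---|---|
| 1 | 53% | 0 | 24.0% | 29.5% | 30.2% |
| 1 | 53% | 0.5 | 22.8% | 28.4% | 29.8% |
| 1 | 53% | 0.8 | 23.2% | 27.6% | 29.4% |
| 2 | 73% | 0 | 25.6% | 39.6% | 39.9% |
| 2 | 73% | 0.5 | 25.1% | 40.6% | 42.1% |
| 2 | 72% | 0.8 | 25.6% | 39.4% | 43.8% |
| 4 | 88% | 0 | 25.0% | 53.0% | 53.1% |
| 4 | 88% | 0.5 | 26.4% | 55.8% | 57.4% |
| 4 | 88% | 0.8 | 25.3% | 53.8% | 60.8% |

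The simulation error is √(0.5 × 0.5/2000), about 1.1 points near 50% power. Repeat simulations differ by a point or two. For correlated counts the working figures are about 30%, 41–45% and 56–61%; a 10,000-run repeat of this model gave 29%, 42–44% and 55–61%. In the same repeat, with m = 0.5 (about 35% of controls making a mistake), none/any gave 18% and rank ANCOVA 19%. With no treatment effect, rank ANCOVA rejected in 4.4–5.8% of runs in the 2,000-run scenarios.

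**4. Where the gain comes from.** In the last row of the table, keeping the count adds 53.8 − 25.3 = 28.5 points and the baseline covariate a further 60.8 − 53.8 = 7.0. In the first row the two steps add 5.5 and 0.7 points. Keeping the count matters most, and the covariate adds 0 to about 7 points.

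**The case against.** The strongest reply is that the plan calls this comparison descriptive and adds it after a Stroop-time analysis that is baseline-adjusted. None/any is easy to read, and the unadjusted comparison is valid. All of this stands and keeps the severity low. It does not restore the discarded information, and p-values on accuracy will still be produced.

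A second reply is that the size of the loss rests on assumed rates. That also stands. If few patients make mistakes, almost nothing is lost. The loss would also be smaller if the treatment mainly changed whether any mistake occurs and not how many.

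Three stronger readings are tempting, and the documents support none of them:

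- **The chi-square approximation fails at 22 per arm.** A reader might infer this from the rule on expected counts, and from the plan's choice elsewhere: "The Stanford Sleepiness Scale will be analysed using descriptive two-sided t-test and Fisher’s exact test". Whether the rule is breached depends on a mistake rate that the documents do not give. Even where it is breached, the uncorrected test stays at or below 0.0519, and Fisher's test would only lower power.
- **Preoperative differences bias the comparison.** Patients are randomized after the baseline test, so such differences arise by chance and the test's error rate already allows for them. Omitting baseline costs precision only.
- **Adjustment is worth 33–96% more patients.** That follows from 1/(1 − ρ²) − 1 with ρ of 0.5 to 0.7. The formula belongs to a linear model of a continuous outcome, and the documents give no correlation. For counts like these the covariate's own contribution is much smaller.

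**Conclusion.** The point holds as a loss of precision. Mistakes are dichotomised and a baseline count already on the forms goes unused, in contrast to the handling of Stroop time. Under the assumptions above, a halved mean count would be detected with power of about 25% by none/any. Rank ANCOVA would reach about 30%, 41–45% or 56–61% as the share of controls making a mistake goes from about 53% to 73% to 88%. Near 35% the two are practically equal.

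The direction is secure, since rank ANCOVA was not materially less powerful in any scenario examined and kept its level near 5%. The size is only indicative, because the mistake rates, the spread between patients and the pre/post correlation are all assumed. The co-primary analyses and the sample size are untouched, so severity is low.

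**What to change.** In section 5, Statistical consideration, specify that the postoperative number of mistakes is analysed separately for word reading and colour naming by rank-based ANCOVA, with the preoperative number for the same task as covariate. Keep none versus any, with its chi-square test, as the descriptive summary. State that it refers to the postoperative visit, that it is given per task, and whether a continuity correction is used.

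No new data, visits or forms are needed. The cost is a little more analysis and an effect measure on ranks that is less directly interpretable than a proportion, which is a reason to keep the none/any table beside it.

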**Patient’s selection, Informed consent, Stroop test**

**Surgery, Wound closure**

**ABG**

**< 2 hours**

**Cranial CT scan with image reconstruction**

**Intracranial air collection of 30 ml or more?**

**Yes No excluded**

**randomization**

**Group 1 Group 2**

**Ventilated with FiO2 100’% weaned off anaesthesia,**

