**via the ETT extubation, ABG**

**3 hours**

**weaned off anaesthesia,**

**extubation, ABG**

**If necessary, further O2**

**via the ETT**

**primary endpoints:**

**cranial CT scan at 24 h after ventilation with FiO2 100’%**

**secondary endpoints:**

**Stanford Sleepiness Scale,**

**Stroop test**

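### The Stanford Sleepiness Scale appears to be rated only after treatment and is compared without a baseline; one preoperative item would allow adjustment and a description of change at almost no cost

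*Combined protocol and SAP*

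**What the plan says.** All references are to the combined protocol and SAP.

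- **Aim.** Under Study objectives, the effect of hyperoxia is to be assessed on attention (Stroop test) and "on alertness, as noted on the Stanford Sleepiness Scale, will be compared and analyzed". The two are set out as parallel aims.
- **Schedule.** The first box of the study flow chart reads "Patient’s selection, Informed consent, Stroop test". The entry "Stanford Sleepiness Scale" appears once, with the Stroop test, among the secondary endpoints next to the follow-up CT.
- **Timing in the text.** Section 3 (Randomization procedure) gives two times for the Stroop test: "The Stroop color-word interference test will be performed one day before surgery and 24 hours after surgery by an Investigator, which is blinded". It gives none for the sleepiness scale.
- **Forms.** The attachments hold separate preoperative and postoperative Stroop sheets. There is one sleepiness sheet, with a blank date and no phase label. It is a single self-rated item scored 1 to 7, with X for asleep.
- **Analysis.** In section 5 (Statistical consideration), the primary endpoints are baseline-adjusted: "Both primary endpoints will be analysed using an analysis of covariance (ANCOVA) including the respective baseline values". Stroop time differences are handled the same way: "postoperative – preoperative) will be analyzed in line with the primary endpoints". The sleepiness scale has its own sentence: "The Stanford Sleepiness Scale will be analysed using descriptive two-sided t-test and Fisher’s exact test".

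**The concern.** Attention and alertness are presented as companion outcomes, but only attention has a preoperative measurement and an adjusted analysis. The plan gives no reason for the difference. Sleepiness is a subjective self-rating, and patients may differ in where they place themselves on such a scale. Without a preoperative rating, three things are lost:

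- change in alertness cannot be reported for either arm;
- comparability of the arms on this outcome before treatment cannot be shown;
- any part of the spread in postoperative ratings that a preoperative rating would have explained stays in the error term.

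An analysis choice can be revised before the data are examined. A preoperative rating that was never taken cannot be recovered.

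**Working it through.** **The plan's own figures.** The plan gives no effect size, SD or power for the sleepiness scale. The only planning figures are those for the co-primary endpoints (under Patients selection), and they supply the arm size used below. With two-sided 5% error and 90% power, n per arm = 2(1.960 + 1.282)² × (SD/difference)²:

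- air volume change: 2 × 10.51 × (16.3/16.6)² = 20.3, so 21; the t-based solution is 21.27, so 22, as stated;
- absorption rate: 2 × 10.51 × (0.96/1.37)² = 10.3, so 11; the t-based solution is 11.37, so 12, as stated.

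Both stated figures reproduce, and 22 per arm is taken as given.

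**Chance baseline difference.** In SD units, its standard error is √(2/22) = 0.30, with a 95% range of about ±1.96 × 0.30 = ±0.59. The chance of an absolute difference of at least 0.3 SD is about 0.32; for at least 0.5 SD it is about 0.10.

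**What reaches the comparison.** Let r be the correlation between the preoperative and postoperative ratings. The documents do not give it, so it is assumed over a range. Equal SDs at the two times are also assumed. Then:

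- shift in the unadjusted comparison from a 0.30 SD imbalance: 0.30 × r;
- variance of the baseline-adjusted (ANCOVA) comparison relative to post-only: 1 − r²;
- equivalent patients per arm: 22/(1 − r²);
- variance of a raw change score relative to post-only: 2(1 − r).

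| Assumed r | Shift (SD) | ANCOVA variance | Equivalent n per arm | Detectable difference, 80% power (SD) | Change-score variance |
|---|---|---|---|---|---|
| 0.1 | 0.03 | 0.99 | 22.2 | 0.84 | 1.8 |
| 0.3 | 0.09 | 0.91 | 24.2 | 0.81 | 1.4 |
| 0.5 | 0.15 | 0.75 | 29.3 | 0.73 | 1.0 |
| 0.7 | 0.21 | 0.51 | 43.1 | 0.60 | 0.6 |

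The detectable difference is (1.960 + 0.842) × √(2(1 − r²)/22). Without adjustment it is 0.84 SD.

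**Cost of estimating the slope.** With 44 patients, the ANCOVA variance is multiplied by about 1 + 1/(44 − 4) = 1.025. The factors become 1.015, 0.933, 0.769 and 0.523. Adjustment breaks even at r = √(1 − 1/1.025) = 0.16, so at r = 0.1 there is no net gain and a loss of about 1.5%.

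**Choice of analysis.** A raw change score is noisier than the post-only comparison whenever r is below 0.5. ANCOVA has the smaller variance at every r in the table.

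**The case against.** The strongest reply is that nothing here is invalid. Allocation is random, so a comparison of postoperative ratings is unbiased, and the t-test's standard error already contains the chance baseline variation. The stated aim is a comparison between arms, not a report of change. The outcome is secondary and its tests are called descriptive. All of this stands.

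A reader might go further than the documents allow in three ways.

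- **That the plan states a postoperative-only rating.** No sentence says so. It is inferred from the flow chart, whose layout is partly lost in the available text, from the single form and from the analysis sentence. An unlabelled form could be used at either time. Postoperative-only is the natural reading. If a preoperative rating was intended, it is missing from the schedule and the analysis, and the same edit is needed.
- **That a 0.3 SD imbalance, expected in about one trial in three, is the error in the result.** Only r times the imbalance carries over: 0.03 to 0.15 SD for r between 0.1 and 0.5.
- **That the gain in precision is assured.** The item asks how the patient feels at that moment, and surgery and anaesthesia lie between the two ratings. A low correlation is plausible, and then adjustment gains next to nothing.

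What survives is narrower. Alertness is treated differently from attention without a stated reason. A preoperative rating would allow change to be described whatever r turns out to be, and would add precision if r is moderate.

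**Conclusion.** The point holds as a cheap improvement, not as an error. As the documents read, sleepiness appears to have no preoperative rating and is compared unadjusted, while the Stroop time and the co-primary endpoints are baseline-adjusted. The cost is some precision and the ability to describe change; validity is not affected.

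The size depends on an assumed correlation. The variance reduction is about 1%, 9% or 25% at r = 0.1, 0.3 or 0.5, before the small cost of estimating the slope, which cancels the gain at the lowest value. Priority is low: no sample size or confirmatory claim rests on this scale, and the conclusion on intracranial air is untouched.

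**What to change.** 1. **Schedule.** Add the sleepiness scale to the first flow-chart box, beside the Stroop test, and state in section 3 when the scale is rated before and after surgery. The session on the day before surgery already exists and precedes randomisation, so allocation cannot influence the rating.
2. **Forms.** Provide preoperative and postoperative versions of the sheet, as is done for the Stroop test.
3. **Analysis.** In section 5, compare the postoperative rating between arms by ANCOVA with the preoperative rating as covariate, and report the estimate with its 95% confidence interval. Summarise change by arm descriptively, but do not test the raw change score. Fisher's exact test can stay as a descriptive supplement. State how a rating of X is handled; the planned t-test needs that rule as well.

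**Cost.** One extra self-rated item at an existing session, a form label and a few lines of text. Patients later excluded for too little intracranial air would also complete the item, as they already do the Stroop test. The downside is little or no gain in precision if the correlation is low.
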